#### Secondary outcomes

Table 1 gives an overview of the secondary outcome measures in the effect evaluation. For these outcome measures, at discharge from GR, mean differences between the intervention and control group will be assessed.

**Table 1 Tab1:** Secondary outcome measures in the FIT-HIP trial

Domain	Assessment	Description	Time point(s)
Physical functioning and activity	Barthel index [40]	Activities in daily living. Measures (in)dependence in personal care (eating, dressing, bathing, going to the toilet) and mobility.	BA, DA, FU1, FU2
	Functional ambulation categories [41]	Evaluates ambulation ability, describing the degree of human support the person needs when walking.	BA, DA, FU1, FU2
	10 meter walk test [42, 43]	Assesses walking function/speed.	BA, DA
	Activity restriction due to fear of falling	Assessed in questionnaire, asking if participant has experienced restriction of activity due to the fear of falling.	BA, DA, FU1, FU2
Falls, complications and health care service usage	Falls (and fall-related injury)	Number of fall incidents and medical attention required as a result of the fall. Assessed using monthly fall calendars.	BA, DA, FU1, FU2
	Complications during GR	Number and type of complication occurring during GR. Assessed by elderly care physician (ECP) in monthly calendars.	Until discharge from GR
	Hospital (re)admission	Number of hospital readmissions and days in hospital. Assessed by ECP in monthly calendars during GR and questionnaire at discharge from GR. Assessed by participants using questionnaire in FU.	DA, FU1, FU2
	Mortality		DA, FU1, FU2
	Healthcare consumption after discharge	Number of contacts with health and community services. Assessed by participants using questionnaire in FU.	FU1, FU2
Other outcome characteristics of GR	Duration of admission to GR	Number of days admitted to GR. Assessed by ECP (questionnaire).	DA
	Total amount of therapy in GR	Number of hours of physiotherapy and of contact with ECP. Assessed by physiotherapists in weekly calendars and by ECP in monthly calendars.	Until discharge from GR
	Discharge location	Location of the residence to which participant is discharged after GR. Assessed by ECP (questionnaire).	DA
Health-related quality of life	EuroQol 5D (EQ5D) [44]	The three-level EuroQol 5D (EQ-5D) is a standardised instrument for measuring generic health status. It can be used for calculating quality adjusted life years (QALYs), for the economic evaluation.	BA, DA, FU1, FU2

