Participation	The Utrecht Scale for the Evaluation of Rehabilitation-Participation. (USER-P) [45]	Assesses (limitations in) participation in relation to health problems.	BA, FU1, FU2

*BA* baseline assessment (pre-intervention), *DA* discharge assessment (post-intervention), *FU1* follow-up 1 assessments, 3 months after discharge from GR, *FU2* follow-up 2 assessments, 6 months after discharge from GR, *ECP* elderly care physician, *GR* geriatric rehabilitation (multi-disciplinary inpatient rehabilitation programme), *EQ-5D* EuroQol 5D, *USER-P* Utrecht Scale for the Evaluation of rehabilitation - participation

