#### Additional variables

Table 2 gives an overview of the additional variables assessed in this trial.

**Table 2 Tab2:** Additional variables assessed in the FIT-HIP trial

Domain	Assessment	Description	Time point(s)
Socio-demographics	Age, gender, marital status, type of residence prior to hip fracture		BA
General health and physical functioning	Functional comorbidity index (weighed) [46]	Assesses 18 comorbid conditions and their effect on physical functioning.	BA
	Medication use	Number and type of medication used by participants. Assessed by ECP (questionnaire).	BA, DA
	Assistive walking device	Type of assistive walking aid, used for indoor and outdoor usage. Assessed by questionnaire.	BA
	Use of formal care (home care) and informal care (given by relatives/volunteers)	Assessed by questionnaire.	BA, FU1, FU2
	Previous fall frequency	Number of falls in 6 months prior to hip fracture.	BA
	Handheld grip strength	Evaluated with dynamometer.	BA
	Nutritional status: Body Mass Index	Calculated by dividing bodyweight in kilograms by length in meters squared.	BA, DA
	Numeric Pain Rating Scale (NPRS) [47]	Assesses intensity of pain on an 11-point scale (0 –10).	BA, DA, FU1, FU2
Hip fracture (related) characteristics	Type of fracture, operation, weight-bearing capacity	Assessed by ECP (questionnaire).	BA
	Duration of hospital admission due to hip fracture	Number of days in hospital.	BA
	Complications during hospital admission due to hip fracture	Number and type of complications. Assessed by ECP (questionnaire).	BA
Neuropsychological factors	Mini Mental State Examination (MMSE) [48, 49]	Screens for cognitive disorders and dementia	BA
	Geriatric Depression Scale, 8-item (GDS-8) [50]	Short adapted version of the GDS-30. Developed to screen depression in nursing home population.	BA
	Hospital anxiety and depression scale – subscale anxiety (HADS-A) [51]	Screens for anxiety.	BA
	Utrecht Coping List; subscales active and passive coping. (UCL) [52]	Assesses coping mechanism. Questionnaire assesses how a person deals with problematic situations in general.	BA
	Pittsburgh Rehabilitation Participation Scale [53]	Participation/motivation for physiotherapy (PT) during GR.	During every session of PT until discharge

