### Economic evaluation

The economic evaluation consists of a cost analysis and a cost-utility analysis, both with a 6-month time horizon after discharge from GR. Costs will be measured from a healthcare perspective. In the cost-utility analysis, the difference in healthcare costs between the strategies will be compared to the difference in Quality-Adjusted Life Years (QALYs, calculated using the 3-level Dutch EQ-5D tariff [38] and the visual analogue scale for health). Estimated healthcare costs will include the costs of the FIT-HIP intervention (estimated from the study registration) and other healthcare utilisation (estimated using quarterly questionnaires filled in by the patients). Other healthcare utilisation will include care provided by general practitioners, consultations of medical specialists and paramedics, home care, informal care, hospitalisation, and residential care. A cost-price analysis will be performed for the FIT-HIP intervention; other healthcare items will be valued using standard prices.

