### Data analyses

Differences between the intervention and control group in characteristics of participants at baseline will be tested with chi-square tests for categorical variables, Mann-Whitney *U*-test for continuous variables with skewed distributions, and one-way ANOVA for normally distributed continuous variables. Given the hierarchical data structure, multilevel analyses will be used for continuous outcomes, and logistic Generalized Estimated Equation (GEE) analyses for dichotomous outcomes. Logistic GEE is preferred to logistic multilevel analyses because of the instability of the latter. Analyses will be based on an intention-to-treat principle and the level of significance will be set at *p* < 0.05. Missing data will be handled as missing (no imputation). Multilevel analyses will be performed with MLwiN. All other analyses will be performed with IBM SPSS statistics.

With regard to the qualitative data (assessed for the process evaluation), these will be analysed by means of coding techniques based on transcriptions of the qualitative interviews. In the economic evaluation, group averages will be compared using unequal-variance t-tests, according to the intention-to-treat principle. Costs will be compared to QALYs using net-benefit analysis. Multiple imputation will be used to account for missing values. Sensitivity analysis will be performed on the time horizon (base case 6 months vs. 12 months) and the utility measure (base case Dutch EQ-5D tariff vs. visual analogue scale for health).

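### The economic evaluation compares QALYs and costs by t-tests that cannot use the EQ-5D and care-use values collected before treatment, so precision is lost and imbalance at entry goes uncorrected.

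*Protocol article*

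**What the plan says.** The Economic evaluation section plans a cost analysis and a cost-utility analysis over six months after discharge, in which "the difference in healthcare costs between the strategies will be compared to the difference in Quality-Adjusted Life Years". Data analyses then fixes the method: "In the economic evaluation, group averages will be compared using unequal-variance t-tests, according to the intention-to-treat principle". It continues: "Costs will be compared to QALYs using net-benefit analysis" and "Multiple imputation will be used to account for missing values". Two sensitivity analyses follow, on the time horizon and on the utility measure. No covariate or regression is named for any of these steps. The multilevel and GEE models in the same section are given for continuous and dichotomous outcomes; the economic evaluation then receives its own method.

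The relevant entry data are collected. In Table 1 the EQ-5D is taken at BA, DA, FU1 and FU2, with the remark "It can be used for calculating quality adjusted life years (QALYs), for the economic evaluation". The table footnote defines BA as "baseline assessment (pre-intervention", that is, before treatment starts. Table 2 lists "Use of formal care (home care) and informal care (given by relatives/volunteers" at BA, FU1 and FU2. Care of this kind is part of the outcome, since the costed items include "consultations of medical specialists and paramedics, home care, informal care, hospitalisation, and residential care".

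**The concern.** Later utility and later care use plausibly depend in part on the patient's state at entry. A comparison of group averages leaves that variation in the error term. It also lets any difference between arms in entry health carry over, in proportion to the slope, into the QALY difference and from there into net benefit.

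The design makes such a difference more likely than in an individually randomised trial of this size. Eleven units from different care organisations are allocated 6 v 5. Physiotherapists in the intervention units are trained before recruitment starts, so patients are screened and included after their unit's allocation is known to its staff. Eligibility rests partly on a self-rated question, and inclusion on willingness to take part.

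Nothing else in the article corrects for this. Duration of rehabilitation, amount of therapy and performance of the intervention components, named under Duration of the FIT-HIP intervention as possible confounders, all arise after allocation. The planned tests of baseline differences have no stated consequence for the economic comparison. Multiple imputation fills gaps in the data; it does not adjust the contrast between arms.

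**Working it through.** **The plan's own figures.** The article gives no power, SD or expected difference for QALYs or costs. Its POMA calculation supplies the cluster inputs and reproduces:
- n = 2 × (1.96 + 0.84)² × (6.0/3.8)² ≈ 39.1, so 40 per group.
- Design effect = 1 + (15 − 1) × 0.05 = 1.70, and 40 × 1.70 = 68.
- With 10% loss, 68 × 1.1 ≈ 75 or 68/0.9 ≈ 76, against the stated 75.

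**Inputs for the check.**
- From the article: 6 v 5 units of at most 15, so 90 v 75 patients; ICC 0.05, stated for POMA and assumed here for EQ-5D; a six-month horizon (0.5 year).
- Assumed, because the article is silent: EQ-5D SD 0.20-0.30; slope of later utility on admission utility 0.3-0.5; QALY SD 0.10-0.15.

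**Step 1: chance imbalance at entry.** In SD units the standard error of the arm difference in admission EQ-5D is √[1.70 × (1/90 + 1/75)] = 0.204. In EQ-5D units this is 0.204 × 0.20 = 0.041 to 0.204 × 0.30 = 0.061. A gap above 0.2 SD has probability 33%, against 20% if the ICC were 0.

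**Step 2: effect on the QALY difference.** Shift = imbalance × slope × 0.5 year.
- Low end: 0.041 × 0.3 × 0.5 ≈ 0.006.
- High end: 0.061 × 0.5 × 0.5 ≈ 0.015.

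**Step 3: implied correlation of admission EQ-5D with QALYs.** r = slope × EQ-5D SD × 0.5 / QALY SD.
- Low inputs together: 0.3 × 0.20 × 0.5 / 0.10 = 0.30.
- High inputs together: 0.5 × 0.30 × 0.5 / 0.15 = 0.50.
- Crossing the inputs widens the range to 0.20 (0.3 × 0.20 × 0.5 / 0.15) and 0.75 (0.5 × 0.30 × 0.5 / 0.10).

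The shift in step 2, as a share of the standard error of the QALY difference (0.204 × 0.10 = 0.020 to 0.204 × 0.15 = 0.031), is this same r.

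**Step 4: precision gained by adjusting.** Residual variance falls by r², the interval narrows by 1 − √(1 − r²), and the equivalent gain in patients is 1/(1 − r²) − 1.

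| r | Variance removed | Interval narrower by | Equivalent gain in patients |
|---|---|---|---|
| 0.3 | 9% | 5% | 10% (165 as if 181) |
| 0.5 | 25% | 13% | 33% (165 as if 220) |

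**Step 5: simulation.** In 6,000 null trials with 11 units of 15 and ICC 0.05, the unadjusted estimate correlated with the entry gap at 0.3 and 0.5 when r was 0.3 and 0.5; the adjusted estimate correlated at about 0. The standard error fell from about 0.20 SD to 0.193 and 0.180 SD.

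**Costs.** The same formulas would apply, but the article gives nothing from which to choose a correlation between care use at BA and total cost. The total also contains hospitalisation, residential care and the intervention itself. No figure is offered.

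**The case against.** **The comparison is not biased by design.** A reader might infer that omitting the covariate makes the QALY result biased. Under sound randomisation and recruitment it does not, and a standard error valid for clusters already includes chance imbalance. This objection stands. What remains is lost precision and a shift in the single trial actually run. Differential recruitment is possible, but the article shows none; it has patients enter in order of admission, eligibility and willingness, and only willingness and the self-rated screening question leave obvious room for it.

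**An entry imbalance need not decide the sign.** It is tempting to say that the expected QALY difference is small enough for imbalance to reverse it. The article gives no expected QALY difference, so that cannot be claimed.

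**Admission EQ-5D is a predictor only.** The horizon starts at discharge, after an average stay of six weeks. If QALYs are counted from there, admission utility is not part of the area being summed, and the case for adjustment rests on the slope. This also stands: the slope is assumed, and at r = 0.3 the gain is modest.

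**A condensed article leaves detail to other documents.** That would answer silence about covariates. Here the test itself is named, and it is one that cannot carry a covariate. The evaluation is, however, the last of four secondary objectives and has no power calculation, which limits the weight of the point.

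**Conclusion.** The point holds as a free improvement in efficiency and in robustness to imbalance. It does not show that the planned comparison is invalid for want of adjustment. The stated t-tests leave unused entry data that the trial already collects, and no other section adjusts the economic comparison for them.

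Under the stated assumptions, one SD of chance imbalance moves the 6-month QALY difference by about 0.006-0.015, and adjustment is worth about 10-33% more patients. A larger gain should not be read into this. It would need a correlation above 0.5, which these inputs reach only when a high slope and a high EQ-5D SD are paired with a low QALY SD. The opposite pairing gives 0.2, with almost no gain. For costs the direction of the argument is the same, but its size is unknown.

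**What to change.** Replace the t-tests by a regression of QALYs, costs and net benefit that accounts for clustering by unit, for example a multilevel model as already planned for the continuous clinical outcomes. Include arm and the admission (BA) value as covariates:
- BA EQ-5D (Dutch tariff) for QALYs and net benefit.
- BA formal and informal care use for costs and net benefit.
- The BA visual analogue score in the sensitivity analysis on that measure, if it is collected at BA. The tables do not name it, so this needs confirming.

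Use the BA value and not the discharge EQ-5D, because discharge comes after allocation and treatment. Report the unadjusted, cluster-aware difference as a sensitivity analysis. The planned multiple imputation can stay.

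An ordinary regression with these covariates would not be enough. Ignoring the units is a separate fault of the same sentence: with a design effect of 1.70, a nominal 5% test has a true level of about 2 × [1 − Φ(1.96/√1.70)] = 13%.

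The cost is a change of wording and a few lines of code. Apart from the visual analogue score, whose BA collection is unconfirmed, no new data are needed. The only presentational price is that adjusted means replace simple averages in the main economic table.

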## Discussion

At present, the functional recovery after a hip fracture in frail older adults is limited, resulting in a considerable amount of long-term disability. Therefore, a hip fracture has major consequences for individual patients, as well as for society, due to the costs of healthcare and the burden on caregivers. Based on the current literature, only a few factors influencing functional recovery after hip fracture could prove to be modifiable. As fear of falling is highly prevalent in hip fracture patients and leads to avoidance of activity, it is probably a significant factor contributing to limited recovery after hip fracture. To our knowledge this is the first RCT to evaluate the effect of treatment of fear of falling in this population. This multicentre cluster RCT will provide insight into whether targeted treatment of fear of falling during geriatric rehabilitation after hip fracture, using the FIT-HIP intervention, is effective in reducing fear of falling and associated avoidance of activities and, therefore, improving functional outcome after hip fracture.

The key component in this trial, guided exposure, is based on the principles of cognitive behavioural therapy. It encourages the systematic confrontation of feared stimuli (situations), in a graded approach. It is the preferred treatment in various types of anxiety disorders, including phobias. In the FIT-HIP programme, the guided exposure is used in conjunction with psycho-education and cognitive restructuring. The programme has been developed together with experts that developed a treatment programme on fear of falling in community-dwelling older adults, which was shown to effectively reduce the fear of falling [21–26].

Because the FIT-HIP programme is integrated in usual care, the additional costs are expected to be limited. In an earlier phase we conducted a small pilot study, aimed at testing the FIT-HIP training and the feasibility of the intervention for healthcare professionals and participants. The additional time spent on therapy for the purpose of this intervention appeared to be limited in the pilot, but will become clear after the evaluation of the intervention. Also, guided exposure was easily integrated in the usual care. Although the principles of guided exposure are often practiced in usual care, they are not generally as structured and intentional as in this intervention.

A strength of this study is that the feasibility for healthcare professionals and patients will be evaluated through a process evaluation. Cost effectiveness will also be assessed. If this intervention proves to be (cost)effective in improving functional outcome after hip fracture and is feasible, it could offer major benefits for individual patients, their (family) caregivers and for society.

This study also has some challenges. Cluster randomisation was chosen as the study design, as the risk of contamination of the FIT-HIP intervention on usual care would be too substantial in view of the complex nature of the intervention. All participating recruitment sites (post-acute GR units) employ a standardised care pathway for patients with hip fracture. This care pathway contains formalised agreements on the content of the multidisciplinary rehabilitation process [39]. As the post-acute GR units are all part of different Dutch care organisations, there could be subtle differences in the usual care for hip fracture patients. These differences (quantity and quality of the received therapy) will be assessed in the process evaluation.

A second challenge in this study, is the blinding. As the FIT-HIP intervention is compared to ‘care as usual’, blinding is only partially possible. Generally, participants should not be aware of what usual care is and what the addition of the FIT-HIP intervention could be. If, however, the usual care does not take note of the fear of falling, the participant could suspect being allocated to the control group. To limit this effect, all participants receive an information brochure on fear of falling and self-help possibilities. Educational interventions alone, aimed at increasing knowledge about fall prevention, have not proven to be effective in fall prevention and we therefore do not expect that this will contaminate the effect of the intervention [31]. The healthcare professionals (physiotherapists, psychologist and nursing staff) receive specific training for conducting the FIT-HIP treatment and are therefore aware of allocation; however, they are instructed not to inform the participants, family or research assistants. Outcome assessors (research assistants) are blinded to allocation.

In conclusion, this study will provide insight into whether fear of falling is modifiable in the rehabilitation process after hip fracture. The results of this trial will be disseminated in peer-reviewed journals and via professional and scientific conferences.

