**Methods/design:**

This multicentre cluster randomised controlled trial will be conducted among older patients with hip fracture and fear of falling who are admitted to a multidisciplinary inpatient geriatric rehabilitation programme in eleven post-acute geriatric rehabilitation units. Fifteen participants will be recruited from each site. Recruitment sites will be allocated by computer randomisation to either the control group, receiving usual care, or to the intervention group receiving the FIT-HIP intervention in addition to usual care. The FIT-HIP intervention is conducted by physiotherapists and will be embedded in usual care. It consists of various elements of cognitive behavioural therapy, including guided exposure to feared activities (that are avoided by the participants). Participants and outcome assessors are blinded to group allocation. Follow-up measurements will be performed at 3 and 6 months after discharge from geriatric rehabilitation. (Cost)-effectiveness and feasibility of the intervention will be evaluated. Primary outcome measures are fear of falling and mobility.

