### Usual care (control group)

Usual care consists of an inpatient multidisciplinary rehabilitation programme (GR) for patients with a hip fracture. This rehabilitation programme is led by an elderly care physician. It comprises physical therapy sessions focussing on balance and gait exercises, and improving muscle strength. The nursing staff and an occupational therapist are also involved in coaching patients in performing ADL, e.g. going to the toilet, and self-care. Each participating post-acute GR unit employs a care-pathway GR, containing formalised agreements on the contents of the multidisciplinary rehabilitation process, such as therapy intensity and assessments during rehabilitation. In general, a patient will receive 5-6 sessions of physiotherapy per week.

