### Blinding

Both the participants and the independent research assistants assessing the outcome measurements are blinded to the group allocation. They are not aware of what usual care is/should be and what the addition of the FIT-HIP intervention is. Healthcare professionals working at the recruitment sites are aware of the allocation status, as the intervention group has been specifically trained to perform the intervention. They are instructed not to inform the participants, family members and the research assistants assessing outcome measures about the allocation status. The main researcher ([name]) was involved in providing the training for the intervention and therefore cannot be blinded in the initial phase of this trial. For data analysis, the database will be processed to blind data to the initial allocation.

To warrant the blinding of participants in the control group (who receive usual care with possibly no specific treatment for or notice of the fear of falling) a dummy intervention is given in both the control and intervention group. The dummy intervention is an information brochure containing information about fear of falling, its consequences, and possibilities for seeking medical attention or help for this problem. This is regarded as an appropriate dummy intervention, as healthcare strategies directed at reducing risk of falling in older adults that use educational interventions alone, have not proven effective [31]. Therefore, we do not expect this information brochure to have a significant effect on the fear of falling.

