#### Therapist data

In the intervention arm of this trial, physiotherapists will register per session which elements of the intervention were conducted, reasons for deviating from the individual FIT-HIP therapy plan and the duration of the therapy sessions, using weekly calendars as session logs. Also, for each therapy session, the Pittsburgh Rehabilitation Participation Scale is filled in as a measure of the extent of active engagement of the participant in the therapy. At the end of the study, the physiotherapists and psychologists conducting the intervention will be invited to take part in qualitative group interviews to discuss in detail their satisfaction with the (components of the) intervention, experienced barriers applying the intervention and suggestions for improvement. Also, matters concerning participant recruitment and maintaining participant engagement will be discussed.

Other members of the GR team (the elderly physician and nursing staff) will be approached to fill in a short evaluation questionnaire about their general opinion of the intervention and to assess to what extent the individual FIT-HIP therapy plans were routinely discussed in the GR team.

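### The claim that outcome assessors are blinded does not cover the secondary outcomes recorded by the unblinded elderly care physician; of these, complications are the one materially exposed

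*Protocol article*

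**What the plan says.** The article describes assessor blinding in three places.

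- Abstract, Methods/design: "Participants and outcome assessors are blinded to group allocation". No assessor is named and no outcome is excepted.
- Blinding section: "Both the participants and the independent research assistants assessing the outcome measurements are blinded to the group allocation".
- Discussion: "Outcome assessors (research assistants) are blinded to allocation".

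The Blinding section also says who is not blinded: "Healthcare professionals working at the recruitment sites are aware of the allocation status, as the intervention group has been specifically trained to perform the intervention".

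Table 1 (Secondary outcomes) names a different assessor for some outcomes. For complications it reads "Number and type of complication occurring during GR. Assessed by elderly care physician (ECP) in monthly calendars". For hospital (re)admission it reads "Number of hospital readmissions and days in hospital. Assessed by ECP in monthly calendars during GR and questionnaire at discharge from GR"; after discharge, the participants report readmissions themselves. Days admitted to GR and discharge location also come from a questionnaire completed by the elderly care physician (ECP). The text introducing Table 1 says that the arms will be compared on these outcomes at discharge.

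On the physician's role, the Usual care section says "This rehabilitation programme is led by an elderly care physician". The Therapist data section counts the physician as a member of the GR team and, in the intervention arm, asks for an opinion of the programme: "Other members of the GR team (the elderly physician and nursing staff) will be approached to fill in a short evaluation questionnaire".

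**The concern.** A reader of the abstract will take it that every outcome was assessed by someone who did not know the allocation. The Discussion supports this by treating outcome assessors and research assistants as the same people. For the outcomes that Table 1 gives to the physician, the protection is absent.

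Complications are where this can change a result. Recording one requires a decision that an event is a complication and is worth an entry. A physician who knows that the unit delivers graded exposure to feared activities may watch more closely and record more, or may favour the programme and record less. The direction cannot be predicted.

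Cluster randomisation makes this harder to detect. Each unit, and so its recording physician, is in one arm only. A recording habit tied to allocation coincides with treatment, and neither the multilevel nor the GEE analysis can separate the two. Blinding the database for analysis, which the Blinding section plans, comes too late to help.

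**Working it through.** **Who assesses what, and who knows the allocation**

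1. Blinded assessors: the independent research assistants (Blinding; Discussion).
2. Unblinded: healthcare professionals at the recruitment sites (Blinding).
3. The ECP is one of these professionals. The role leads the programme (Usual care) and is asked to evaluate the intervention as a team member (Therapist data). The Discussion's list of trained staff who know the allocation names physiotherapists, psychologist and nursing staff but not the physician. The conclusion therefore rests on the general sentence in the Blinding section, together with these two places.
4. Outcomes assessed by the ECP in Table 1: complications during GR, in-stay hospital readmission, days admitted and discharge location. ECP contact time, part of the therapy-amount row, is also recorded by the ECP.
5. From 2, 3 and 4, these outcomes have an unblinded assessor. The article describes no blinded review of them.
6. The primary outcomes, POMA and FES-I, are not assigned to the ECP anywhere.

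**How exposed each outcome is**

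- Complications: number and type, which need judgement. Exposed.
- Number of readmissions, days admitted, discharge location: largely administrative facts. Knowing the allocation might influence the decision to refer or discharge, but that is not an assessment error, and a blinded assessor would not prevent it.

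**Size (illustration only)**

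The documents give no complication rate and no recording completeness, so both are assumed. Let the true rate p be the same in both arms, with recording complete in one arm and a fraction s complete in the other. The false difference is p × (1 − s).

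- Smallest: p = 0.20, s = 0.90 gives 0.20 × 0.10 = 0.02, or 2 points.
- Largest: p = 0.40, s = 0.70 gives 0.40 × 0.30 = 0.12, or 12 points.
- The apparent risk ratio equals s, so 0.70 to 0.90.

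With both arms incomplete and p = 0.40: 0.40 × 0.90 = 36% against 0.40 × 0.80 = 32%, or against 0.40 × 0.70 = 28%. The false difference is 4 or 8 points.

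**Against the precision of the trial**

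Six intervention and five control units of 15 give 6 × 15 = 90 and 5 × 15 = 75 patients. If the ICC of 0.05 stated for POMA is borrowed for complications (an assumption), the design effect is 1 + (15 − 1) × 0.05 = 1.70. The effective numbers are 90 / 1.70 = 52.9 and 75 / 1.70 = 44.1.

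- 36% against 32%: SE = √(0.36 × 0.64 / 52.9 + 0.32 × 0.68 / 44.1) = √0.0093 = 0.096.
- 36% against 28%: SE = √(0.36 × 0.64 / 52.9 + 0.28 × 0.72 / 44.1) = √0.0089 = 0.094.

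The 4 and 8 point distortions are each less than one standard error. On their own they would seldom produce a false significant result, but they shift the estimate and its interval. A larger sample would not remove the shift.

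**The case against.** The strongest reply is that the article does not contradict itself. The Blinding section and the Discussion attach the claim to research assistants, the Discussion concedes that blinding can only be partial, the unblinded status of site staff is disclosed, and Table 1 names the physician outcome by outcome. This largely stands. A reader might infer that the blinding of the research assistants is contradicted, but nothing in the documents supports that. What remains is that the abstract carries no limit, that the Discussion treats research assistants as the only outcome assessors, and that the stated reasons for partial blinding (participants' suspicion, trained staff) never mention physician-assessed outcomes.

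Second, a reader might infer that complications are an open count left to each physician, with no definitions. The article says only that number and type are noted on monthly calendars. The form is not shown, and the full protocol may define the events. No finding rests on this.

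Third, a reader might infer that all the physician-assessed outcomes are equally biased, or that a safety conclusion is undermined. The administrative outcomes are not comparably exposed. The article announces no safety conclusion, and complications appear in Table 1 but in none of the stated objectives.

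Fourth, recording by the treating physician is common when the team delivers the intervention and cannot be masked. This is true. It is a reason to state the fact, not to let the general claim cover it.

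**Conclusion.** The point holds in a limited form. The article claims a property, blinded outcome assessors, that its design lacks for the secondary outcomes recorded by the ECP. This rests on the physician being among the site professionals who know the allocation, which the Blinding, Usual care and Therapist data sections together support.

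The material consequence is confined to the between-arm comparison of complications during GR. The documents do not show that bias will occur, in which direction, or how large it would be; the 2 to 12 point range is purely illustrative. The conclusions on POMA and FES-I are unaffected.

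**What to change.** 1. In the abstract and Discussion, limit the blinding claim to outcomes measured by the research assistants.
2. State that complications, in-stay readmission, days admitted and discharge location are recorded by a physician who knows the allocation.
3. Interpret the complication comparison accordingly: a difference, or its absence, may partly reflect recording.
4. If the full protocol does not already do so, record complications in both arms against one prespecified list of defined events, with an 'other' line so that rare events are not lost.

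Arm-masked coding of the entries is optional. It protects how a recorded event is classified but cannot recover an event that was never entered.

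The cost is a slightly less favourable blinding statement and, where step 4 is needed, a short form. The sample size and the primary analysis do not change.
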